### 2.3. Procedure

In the screening phase, participants will fill in online (via the Qualtrics platform) a non-psychometric self-report questionnaire and several self-report psychometric screening questionnaires for the detection of three unhealthy lifestyles and behaviors: heavy smoking, heavy drinking, and dysfunctional eating behaviors (see Screening measures). Individuals interested in taking part in the research will be informed of the aims and characteristics of the study. If they agree to participate, they will be asked to sign an informed consent online on Qualtrics. Participants who provide written informed consent will be screened, and if suitable to participate, will be subsequently contacted via e-mail or smartphone within 7 days and invited to take part in the experimental phase of the study.

In the experimental phase, participants in each of the three samples will be randomized to the intervention (VR) or control (waiting-list) condition following a “block randomization” method [35]. Before randomization, participants will undergo a brief clinical interview based on the DSM-5-TR criteria conducted by a charted clinical psychologist researcher to exclude the presence of DSM-5-TR psychiatric disorder diagnoses. Participants in the VR group will undergo six 30 min sessions of the VR-based intervention administered using the software H.O.M.E. in the presence of a clinical psychologist (the intervention protocol is illustrated below). Controls (waiting-list group) will not receive any intervention during the study, but they will receive minimal attention from researchers through phone check-up sessions to monitor their symptoms and general well-being. They will also be offered to receive the VR-based intervention after concluding the study.

To test whether changes will be maintained over time, both groups will be re-contacted for follow-ups after 3 and 6 months.

Immediately before the first session of the intervention phase (T0), at the conclusion of the intervention phase (T1), and at the 3 (T2) and 6-month follow-ups (T3), participants of all groups will be asked to complete a series of psychometric self-report questionnaires online (using the Qualtrics platform) (see Outcome measures).

More details about the allocation of participants and the RCT design are shown in Figure 1.

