##### VR-Based Intervention Group

The proposed VR-based intervention will consist of six weekly sessions of approximately 30–50 min. The intervention will take place at the VR laboratory of the Department of Psychology of the University of Bologna. The intervention protocol will be delivered by a clinical psychologist (author [name]).

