#### 2.4.2. Control (Waiting-List) Group

The control group in this study consists of a 6-week waiting-list condition. Participants in this group will not receive VR-based interventions or any other interventions during the study. However, minimal attention from researchers will be paid to controls via phone check-up sessions to monitor their dysfunctional behaviors and general well-being. The phone check-ups will also be carried out by a charted clinical psychologist (author [name]). Controls will also be offered to receive the VR-based intervention after six weeks.

Participants in the WL condition will also be recontacted after 3 and 6 months for follow-ups to assess whether changes will be maintained over time.

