#### 2.5.2. Outcome Measures

Changes in the levels of endorsed unhealthy behaviors will be measured by administering the FTND, AUDIT, SCOFF, and EDE-Q at the beginning (T0) and end (T1) of the VR intervention to the participants of the relative sample, as well as at the 3- (T2) and 6-month (T3) follow-up.

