Moreover, to also take into consideration the possible multivariate nature of the involved variables and the association between dysfunctional behaviors, transdiagnostic factors, and stress, we will perform repeated measures MANOVAs using time (T0, T1, T2, and T3) as a within-subject factor, group assignment (experimental/VR vs. control) as a between-subject factor, and questionnaire scores (one between FTND, AUDIT, or EDE-Q scores depending on the sample, as well as DERS-16, AAQ-II, and MPFI-EA for transdiagnostic factors and DASS-21 for stress) as five dependent variables.

MANCOVAs will also be performed to compare the mean levels of relevant unhealthy behavior (FTND, AUDIT, or SCOFF and EDE-Q scores), transdiagnostic factors (DERS-16, AAQ-II, and MPFI-EA scores), and stress levels (DASS-21-stress scale scores) of the experimental and control (waiting-list) groups of the samples at each assessment time (T1, T2, and T3), adjusting for any differences at T0 and age. In particular, three MANCOVAs will be run (one for T1 scores, one for T2 scores, and one for T3 scores) for each sample relative to the dysfunctional behaviors using group (VR or waiting-list) as an independent variable, questionnaire scores (one between FTND, AUDIT, or EDE-Q scores depending on the sample, the questionnaires DERS-16, AAQ-II, and MPFI-EA for transdiagnostic factors and the DASS-21 for stress) as five dependent variables, and scores at T0 and age as covariates.

All analyses will be performed following an Intention-To-Treat (ITT) approach in order to preserve the randomized design and provide a more conservative estimate of treatment effects.

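### The self-reported baseline (T0) is taken after randomisation to arms that cannot be masked, so knowledge of allocation can affect the baseline used in every efficacy model

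*Protocol article*

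**What the plan says.** Section 2.3 (Procedure) describes an online screening phase followed by an experimental phase in which "participants in each of the three samples will be randomized to the intervention (VR) or control (waiting-list) condition". Within the experimental phase, one step is put ahead of that: "Before randomization, participants will undergo a brief clinical interview based on the DSM-5-TR criteria". The assessment schedule is then "Immediately before the first session of the intervention phase (T0), at the conclusion of the intervention phase (T1", with T2 and T3 at 3 and 6 months. Section 2.5.2 (Outcome Measures) agrees, describing change in behaviour as measured by "administering the FTND, AUDIT, SCOFF, and EDE-Q at the beginning (T0) and end (T1) of the VR intervention".

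The comparison is open by nature: "Controls (waiting-list group) will not receive any intervention during the study", while the other arm attends laboratory sessions with a psychologist.

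Section 2.6 (Data Analyses) uses T0 in four ways:
- in the pairwise time contrasts within the VR arm;
- as a level of the time factor in the repeated-measures ANOVAs;
- as a level of the time factor in the repeated-measures MANOVAs;
- in the MANCOVAs at T1, T2 and T3, "adjusting for any differences at T0 and age".

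Section 2.5.1 (Screening Measures) collects the AUDIT, FTND and EDE-Q before the experimental phase, and their cut-offs decide eligibility. Section 2.5.2 introduces the DERS-16, AAQ-II, MPFI-EA and DASS-21 as T0 to T3 measures.

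**The concern.** A baseline should be a variable that allocation cannot influence. That property is what allows change from baseline, or adjustment for it, to be read as a treatment comparison. Here the fixed order is interview, randomisation, T0, first session. A participant who arrives for a VR session knows the allocation. A participant told to wait may know it too. Stress, emotion regulation, avoidance and self-rated behaviour could all respond to anticipation or disappointment.

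If they do, the arms differ at T0 for a reason other than chance, and that difference carries into each analysis that uses T0. The planned tests of pre-intervention differences cannot help, because they cannot tell chance imbalance from a reaction to allocation. Later repair is limited. Four of the five dependent variables in the MANOVAs and MANCOVAs (DERS-16, AAQ-II, MPFI-EA, DASS-21) have no pre-randomisation value described.

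**Working it through.** **Order of events, from sections 2.3, 2.5.1 and 2.5.2**

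| Step | Data collected | Relative to randomisation |
|---|---|---|
| Online screening | AUDIT, FTND, EDE-Q | before |
| Diagnostic interview | diagnosis | before |
| T0 | relevant behaviour scale, DERS-16, AAQ-II, MPFI-EA, DASS-21 | after, as written |
| T1, T2, T3 | same scales | after |

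No section shown places T0 before allocation.

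**Inputs.** The protocol gives no figure for this effect, so there is none to reproduce. From section 2.2: about 64 participants per sample, two arms, four time points. Assumed, because the documents do not give them: a shift in one arm's mean at T0 of delta SD, a correlation rho between any two time points, equal variances, a 5% test level and no true treatment effect.

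**Bias if the shift affects T0 only**

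- Difference between arms in change from T0: 0 − delta, so the absolute bias is delta.
- Difference at T1 adjusted for T0, with within-arm slope rho: 0 − rho × delta, so the absolute bias is rho × delta.

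At delta = 0.2 and rho = 0.5 these are 0.2 SD and 0.5 × 0.2 = 0.1 SD.

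A simulation (3000 runs per cell, one outcome, N = 64, complete data) agrees. At delta = 0.2 and rho = 0.5 it gave 0.193 and 0.097 SD. Rejection rates with no true effect were:

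| Assumed delta | Bias in change (SD) | Adjusted bias, rho = 0.5 (SD) | Group-by-time rejection, rho = 0.3 / 0.5 / 0.7 | Adjusted T1 rejection, rho = 0.5 |
|---|---|---|---|---|
| 0 | 0 | 0 | 5.1% / 4.6% / 4.9% | 5.7% |
| 0.1 | 0.1 | 0.05 | 6.4% / 6.0% / 7.0% | 5.0% |
| 0.2 | 0.2 | 0.10 | 9.3% / 9.9% / 16.4% | 7.4% |
| 0.3 | 0.3 | 0.15 | 16.2% / 20.7% / 31.2% | 10.6% |

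**If the shift persists.** Suppose a fraction phi of it remains at T1, and the target is the treatment effect apart from this reaction. The bias in change becomes (phi − 1) × delta, which shrinks to zero as phi goes to 1. The adjusted bias becomes (phi − rho) × delta. With delta = 0.2 and rho = 0.5, phi = 0.5 gives 0.1 SD (absolute) for change and 0 for the adjusted contrast. Phi = 1 gives 0 for change and 0.1 SD for the adjusted contrast, now in the opposite direction. The T0-only case is therefore the worst for contrasts against T0.

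**What is not affected.** Contrasts among T1, T2 and T3 do not involve T0. The four-level group-by-time test is affected only through its T0 component.

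**The case against.** Several points on the other side are fair.

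**Disclosure time is not stated.** No sentence says when participants learn their arm. Section 2.3 refers to Figure 1 for allocation details, and that figure is not available here. This limits certainty about practice, but not about the text: nothing shown puts T0 ahead of randomisation, and someone attending a VR session must know the arm by then.

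**Pre-randomisation scores do exist.** A reader might infer that nothing but the interview precedes randomisation. That is wrong: screening AUDIT, FTND and EDE-Q scores come first. They give a partial safeguard for the behaviour outcome, if the analysis uses them.

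**The magnitude is illustrative.** Delta and rho have no source in the documents, and the direction could favour either arm. The EDE-Q refers to the past 28 days, which limits how far recent news can move it. Quoting the bias as a share of the planned effect would suggest a precision that is not there.

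**Three stronger readings are not supported.**

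- That the controls' T0 has no anchor. The Abstract places assessment before and after the waiting period as well as the intervention, and the Introduction gives controls weekly phone check-ups over six weeks.
- That the T0 to T1 interval differs by arm. One could count "The proposed VR-based intervention will consist of six weekly sessions" as 5 × 7 = 35 days and "The control group in this study consists of a 6-week waiting-list condition" as 6 × 7 = 42. Section 2.3, however, gives all groups the same T1 definition, and both phrases are ordinary descriptions of one period.
- That people lost between allocation and T0 undermine the intention-to-treat claim. No such loss rate is given, and an article commonly leaves missing-data handling to the full protocol.

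**Re-anchoring T1 to T3 to randomisation is a trade-off.** It could place T1 before late starters finish, so it forms no part of this point.

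**Conclusion.** The point holds for the placement of T0. On the protocol's own text, the baseline follows randomisation to conditions that participants can tell apart, it is self-reported, and it enters every efficacy model. Adjustment for T0 does not reliably remove the problem, because the covariate itself may be affected.

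The size and direction of any bias are unknown. At an assumed T0-only shift of 0.2 SD and rho = 0.5, it is 0.2 SD for contrasts against T0 and 0.1 SD for T0-adjusted contrasts. The first of these is smaller to the extent that the shift persists. The conclusion rests on the written order of events and on participants knowing their arm by T0. If practice already takes T0 before disclosure, only the wording needs correcting.

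This is an avoidable weakness that is worth correcting. It does not show that the trial's results would be biased by any particular amount.

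**What to change.** Amend sections 2.3 and 2.5.2 so that all participants complete the full T0 battery on Qualtrics after the eligibility interview and before their allocation is drawn or, at the latest, disclosed. With T0 taken then, delta is zero by design. The planned models and sample size stay as they are.

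Where this is not possible, for example for participants already randomised, add a sensitivity analysis with the screening AUDIT, FTND or EDE-Q score as the baseline. This covers the behaviour outcome only. It does not cover DERS-16, AAQ-II, MPFI-EA or DASS-21.

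Cost: a short wording amendment and a change in the order of one online questionnaire, with no extra participants or instruments. The downside is a possibly longer gap between T0 and the first session. That gap could matter, since the article names one psychologist to deliver about 3 × 64 / 2 = 96 courses of six sessions, or about 576 sessions. Randomising each participant close to the planned start keeps it short.

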### 2.4. Interventions

#### 2.4.1. VR Software: H.O.M.E. (How to Observe and Modify Emotions)

H.O.M.E. (How to Observe and Modify Emotions) is a transdiagnostic VR software (vrs.1) developed by a group of clinical psychology researchers (clinical psychologists and psychotherapists [name], [name], and [name] and psychiatrist and psychotherapist [name]) from the Department of Psychology at the University of Bologna. H.O.M.E. can be used by connecting a computer to any VR headset (in this case, an HTC Vive headset will be used for the study). The software offers users the opportunity to move around a virtual environment consisting of a house with four rooms (i.e., kitchen/living room, bathroom, bedroom, and a study; Figure 2) and a garden and to interact with objects representing likely relevant cues for specific at-risk behaviors (e.g., comfort foods for people with eating-related issues; alcohol, pills, and cigarettes for users with substance use disorders; a computer with a gambling interface for those with gambling addictions; videogames and a smartphone for individuals with technology-related addictions). The software includes two separate but interrelated virtual features: an assessment virtual feature (Figure 3) in which users can attribute to each object the emotion they associate with it and its intensity; and an intervention virtual feature (Figure 4) based on the cognitive-behavioral model in which users can access a box containing “psychological resources”, including pictures and descriptions of twelve emotional, social, and behavioral resources that can be used to deal with the emotions previously attributed to the following objects: (1) forgiveness; (2) awareness; (3) physical activity; (4) life purposes; (5) interpersonal relationships; (6) recreational activities (e.g., hobbies); (7) self-esteem; (8) gratitude; (9) transcendence and spirituality; (10) wisdom; (11) autonomy-assertiveness; and (12) self-control. These resources have been derived from theoretical models at the base of third-wave cognitive behavioral therapies (e.g., mindfulness-based therapy, acceptance and commitment therapy, dialectical behavioral therapy, positive psychotherapy, etc.), such as the psychological well-being model of Carol Ryff [36] and the value in action (VIA) classification of the character’s strengths and virtues model [37]. The software is meant to be transdiagnostic since it is designed to tackle the following transdiagnostic factors: emotion regulation (ER) strategies, psychological flexibility, and experiential avoidance, which are meant to be used in the prevention and treatment of several psychiatric disorders (e.g., EDs, substance-use disorders, addictions, etc.) and severe levels of stress under the instructions of a clinical psychologist. The need for a clinical psychologist when using H.O.M.E. represents another innovative aspect of this software, as it allows the inclusion of clinical judgment when using this technological tool in a VR-based intervention. According to the aims of this specific research project, H.O.M.E. will be used to deliver a VR-based assessment and intervention in individuals from the general population who exhibit unhealthy lifestyles and behaviors (i.e., heavy smoking, heavy drinking, and dysfunctional eating behaviors) and are at risk for nicotine dependence, alcohol abuse, or eating disorders.

##### Virtual Reality Devices

The devices used to deliver the VR intervention will include a computer and an HTC Vive VR headset. The HTC Vive headset will be connected to a computer in order to access the VR software used for the study: the H.O.M.E. (How to Observe and Modify Emotions) software (described below). Participants will be able to navigate the virtual environment using the HTC Vive headset and controllers. During the intervention session, the clinical psychologist will also be able to see the participant’s actions in the virtual environment and, therefore, they will be able to give instructions to the participants.

##### VR-Based Intervention Group

The proposed VR-based intervention will consist of six weekly sessions of approximately 30–50 min. The intervention will take place at the VR laboratory of the Department of Psychology of the University of Bologna. The intervention protocol will be delivered by a clinical psychologist (author [name]).

The six VR-based intervention sessions will have different aims and will be divided as follows:(1)Session 1 will focus on gathering information about the participants and instructing them on the use of virtual reality interfaces. During this session, the participants will have the time to familiarize themselves with the H.O.M.E. software VR environment, and the clinician will verify if any motion sickness symptoms or difficulties in using the VR device are reported by participants.(2)Session 2 will focus on the interaction with the objects in the virtual HOME environment that are the most relevant for the participant (i.e., foods, drinks, electronic devices, cigarettes, etc.). During this session, the participant will be asked to attribute to each relevant object the emotions they associate with it and its intensity (this will be performed via the assessment phase of the H.O.M.E. software). CBT-based homework (in particular, filling in an Antecedents, Behavior, Consequences-ABC worksheet throughout the subsequent week) will be given to the participant at the end of the session.(3)Session 3 will focus on recreating critical situations that the patient wrote in the ABC worksheet in the H.O.M.E. software and further discussing the relevant objects and elicited emotions.(4)Session 4 will focus on illustrating to the participants all the psychological/behavioral resources present in the “box of resources”. The participants will then be asked (with help from the clinical psychologist, if needed) to select the resource they think will be the most beneficial to overcome the distressing emotions previously attributed to the critical objects (this is performed using the intervention phase of the H.O.M.E. software). The clinician will also discuss with participants how to use this resource in the real world, and the participants will be asked to apply it in everyday life during the following week as homework.(5)Session 5 will focus on discussing the difficulties participants might have experienced when trying to use the resource in their everyday life, and if needed, additional exercises will be conducted in the virtual environment to better use the resource. Alternatively, the participant might be asked to select an additional resource they would like to explore.(6)Session 6 will focus on re-evaluating the objects the participant previously selected as critical and evaluated in Session 2 to assess possible changes in the intensity and type of emotions attributed to them after using the psychological resources to deal with them in a real-life context.

To test whether changes will be maintained over time, participants will be re-contacted for follow-ups after 3 and 6 months.

#### 2.4.2. Control (Waiting-List) Group

The control group in this study consists of a 6-week waiting-list condition. Participants in this group will not receive VR-based interventions or any other interventions during the study. However, minimal attention from researchers will be paid to controls via phone check-up sessions to monitor their dysfunctional behaviors and general well-being. The phone check-ups will also be carried out by a charted clinical psychologist (author [name]). Controls will also be offered to receive the VR-based intervention after six weeks.

Participants in the WL condition will also be recontacted after 3 and 6 months for follow-ups to assess whether changes will be maintained over time.

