To fill this gap in the literature, researchers and clinicians (clinical psychologists and psychotherapists [name], [name], and [name] and psychiatrist and psychotherapist [name]) from the Department of Psychology of the University of Bologna designed a transdiagnostic VR software and intervention protocol (H.O.M.E.—How to Observe and Modify Emotions) to improve emotion regulation, experiential avoidance, and psychological flexibility in order to make them suitable for several clinical and non-clinical populations. The H.O.M.E. intervention was designed to be a six-session intervention protocol focusing on the assessment of emotions elicited by trigger cues present in the virtual environment (e.g., comfort foods, cigarettes, alcohol, etc.) and the tackling of these emotions through CBT-based exercises to enhance the aforementioned transdiagnostic factors.

In particular, this study presents the research protocol for a randomized controlled trial designed to evaluate the effects of H.O.M.E. VR-based intervention in ameliorating the frequency and severity of unhealthy behaviors (i.e., heavy smoking, heavy drinking, and dysfunctional eating behaviors) and three transdiagnostic factors (emotion regulation, experiential avoidance, and psychological flexibility) levels in individuals of the general population that are considered at risk for nicotine dependence, alcohol abuse, or eating disorders. These experimental groups will be compared to a waiting-list condition consisting of a 6-week duration with weekly phone check-ups. The hypotheses are that H.O.M.E. will prove to be effective in reducing the frequency and severity of unhealthy behaviors as well as improving the transdiagnostic factors, even when compared to the waiting-list condition.

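### The protocol gives two times for offering VR to controls; if the six-week offer is followed, the 3- and 6-month comparisons are no longer VR against an untreated waiting list

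*Protocol article*

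**What the plan says.** The protocol article describes the control arm in three places.

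- **Introduction:** a "waiting-list condition consisting of a 6-week duration with weekly phone check-ups".
- **Section 2.3 (Procedure):** "Controls (waiting-list group) will not receive any intervention during the study", followed by "They will also be offered to receive the VR-based intervention after concluding the study".
- **Section 2.4.2 (Control Group):** "The control group in this study consists of a 6-week waiting-list condition", then "Participants in this group will not receive VR-based interventions or any other interventions during the study", and at the end of the same paragraph "Controls will also be offered to receive the VR-based intervention after six weeks". The next paragraph says that the waiting-list participants "will also be recontacted after 3 and 6 months for follow-ups".

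Section 2.6 tests efficacy against the waiting list by repeated-measures ANOVA and MANOVA over T0 to T3. It adds group comparisons at each later time: "three MANCOVAs will be run (one for T1 scores, one for T2 scores, and one for T3 scores) for each sample". All analyses follow intention to treat. The abstract expects participants to do better than controls both after the intervention and at the follow-ups.

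**The concern.** The two offers cannot both hold if *the study* includes the 3- and 6-month assessments. After the study means after T3. After six weeks means at T1, before both follow-ups.

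Under the six-week offer, controls who accept are treated before T2 but are still analysed as waiting list. If the intervention works and its effect lasts, the between-arm difference shrinks from T1 to T2 and T3 because the controls catch up. A reader of the group comparison could take that for a fading effect, or take the controls' gain for spontaneous recovery. If the effect does fade with time, controls treated more recently could even look better than the VR arm. In each case the randomised comparison with untreated people at follow-up, which the abstract relies on, is lost or diluted.

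**Working it through.** The point rests on the text. The plan has no figure of its own to reproduce here, and the planned size of about 64 per sample is used only as an input.

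**1. Can the statements be reconciled?** There are two readings.

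- *The study* runs to T3. Then the six-week sentence in section 2.4.2 contradicts section 2.3 and also the second sentence of its own paragraph.
- *The study* means only the six-week phase. The wording is then consistent, but controls may be treated before T2 and T3, so the comparison problem is part of the plan.

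**2. Would controls be treated by T2?** The VR course is six weekly sessions (VR-Based Intervention Group). Started promptly at week 6, it ends at about week 11 to 12. The article does not say where the 3 months start:

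- from baseline, T2 is at about week 13;
- from the end of the intervention, T2 is at about week 6 + 13 = 19.

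The course ends before T2 in both cases, and so before T3.

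**3. Which analyses are affected?** There are three MANCOVAs per sample and three samples, so 3 × 3 = 9. Those at T2 or T3 number 2 × 3 = 6. The repeated-measures ANOVA and MANOVA also use T2 and T3. Under intention to treat, treated controls stay in the control arm.

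**4. How much would the difference shrink?** Section 2.2 plans on f = 0.25, which for two groups is d = 2f = 0.5. Assume that this effect lasts and that treated controls benefit equally. Then

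expected T2/T3 difference = 0.5 × (1 − uptake).

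Power for one unadjusted contrast at T2 or T3, by normal approximation, is Φ(d√(n/2) − 1.96). Two-sided alpha 0.05 and 1:1 allocation are assumed, giving 32 per arm, or 22 after 30% drop-out (32 × 0.7 = 22.4). At 25% uptake, for example, 0.375 × √16 = 1.5, 1.5 − 1.96 = −0.46, and Φ(−0.46) = 0.32.

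| Uptake of the offer | Expected difference (SD) | Power, 32 per arm | Power, 22 per arm |
|---|---|---|---|
| 0% | 0.5 | 0.52 | 0.38 |
| 25% | 0.375 | 0.32 | 0.24 |
| 50% | 0.25 | 0.17 | 0.13 |
| 75% | 0.125 | 0.07 | 0.06 |
| 100% | 0 | no difference to detect | no difference to detect |

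**5. Would the group-by-time test reveal the problem?** No. With N = 64, between-time correlation 0.5 (assumed) and sphericity, the noncentrality is λ = 64 × Σ(c²/4) / (1 − 0.5), where c is each time's group difference minus the mean difference.

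- Lasting effect, controls untreated, differences (0, 0.5, 0.5, 0.5): Σc² = 0.1875, so λ = 6.0 and power is 0.51.
- All controls treated after T1, differences (0, 0.5, 0, 0): Σc² = 0.1875, so again λ = 6.0 and power is 0.51.

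The overall interaction test has the same power in both situations, so a significant result would not show which one occurred.

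**The case against.** The best defence is that most of the text supports untreated controls up to T3. Section 2.3 says so twice, and section 2.4.2 says so in the same paragraph as the six-week offer. That sentence may be a drafting slip, in which case deleting it leaves the T2/T3 analyses intact. Figure 1, which section 2.3 cites for the design, is not available here and may show the intended timing. Both points are fair. They do not settle the matter, because the six-week length given in the Introduction and in section 2.4.2 supports the other reading, and a figure would not remove the conflicting sentence.

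Three further points limit the size of the problem:

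- Section 2.6 also plans contrasts among all assessment times within the VR arm. A maintained improvement would show there, so only the between-arm evidence would appear to fade. Those contrasts, however, have no control.
- VR is offered, not imposed, so the dilution depends on uptake, for which the article gives no figure.
- An intention-to-treat comparison at T2/T3 would still be a valid randomised comparison of immediate with delayed offer. It answers a different question from the VR-versus-waiting-list comparison that section 2.6 describes.

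**Conclusion.** The concern holds. The contradiction is in the current text, and the only reading that removes it makes treatment of controls before T2 and T3 part of the plan. Nothing in the article says how treated controls would be handled at those times.

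The consequence is conditional. If VR is offered only after T3, the fault is one wrong sentence. If it is offered at six weeks, the T2/T3 difference shrinks in proportion to uptake, from 0.5 SD to 0.25 SD at half uptake and to zero at full uptake. At full uptake, six of the nine MANCOVAs contain no treated-versus-untreated contrast. These sizes assume a lasting 0.5 SD effect, equal benefit in treated controls and a prompt start at week six. The T1 comparison is sound under either timing.

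This must be fixed, because controls who are treated before follow-up cannot be made untreated again by any later analysis.

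**What to change.** State one timing in sections 2.3 and 2.4.2 and make section 2.6 follow it.

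- **Offer only after T3 (keeps the planned comparisons).** Delete the six-week sentence and say that VR is offered once the 6-month assessment is complete. T2 and T3 remain randomised VR-versus-waiting-list comparisons. The cost is a longer wait for controls.
- **Offer at six weeks.** Limit the VR-versus-waiting-list claim to T1, and take T2 and T3 out of the between-arm ANOVA, MANOVA and MANCOVAs. Report them as follow-up without an untreated control. If a between-arm result at T2/T3 is still wanted, label it immediate versus delayed offer. Amend the expectation in the abstract to match. The cost is the controlled claim about durability.

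Either way, align the participant information and state whether the 3 and 6 months run from baseline or from the end of the intervention. Settle this before controls reach week six. If any already have, record who received VR and when. No extra participants are needed.
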